## Abstract

Background: Brief psychotherapies have been shown to improve clinical symptoms within a limited number of sessions without compromising treatment quality. Objectives: This study aims to test the effects of the experimental Behavioral Analysis Therapy of Feelings (BATF) in a randomized controlled trial design. Methods: This randomized, controlled, assessor-blinded clinical trial compares BATF with Brief Focal Psychotherapy in individuals presenting symptoms of anxiety and/or depression. Participants with substance use disorders, tobacco or alcohol use, pregnancy, or use of oral contraceptives will be excluded. Participants will be randomized in a 1:1 ratio with stratification by clinical condition. Outcomes will be assessed at baseline, Week 4, and Week 13 using the Hamilton Anxiety Rating Scale, the Montgomery–Åsberg Depression Rating Scale, the Patient Health Questionnaire-9, the Generalized Anxiety Disorder-7, and the Pittsburgh Sleep Quality Index. In addition to clinical outcomes, exploratory salivary and blood biomarkers associated with stress, inflammation, and neurobiological function will be evaluated. The trial is registered in the Brazilian Clinical Trials Registry (RBR-10p45rdg) and has Universal Trial Number U1111-1313-4499. Conclusions: This protocol describes a randomized controlled trial comparing BATF with Brief Focal Psychotherapy. The study is designed to generate preliminary evidence on the effects of the intervention in anxiety and depressive symptoms.

## 1. Introduction

Anxiety is linked to impairments in psychosocial well-being, quality of life, and the perception of negative effects associated with depressive symptoms [1]. Mild to moderate anxiety and depressive symptoms may benefit from brief psychotherapeutic interventions, which have demonstrated effectiveness in reducing emotional distress [2]. Treatment selection should be individualized according to symptom severity, diagnostic characteristics, and clinical context, and may include psychotherapy, pharmacotherapy, or their combination when clinically indicated. These interventions are characterized by a limited number of sessions, a focus on the patient’s primary complaint, and clearly defined objectives aimed at achieving improvement within a short period of time. Examples of brief psychotherapeutic approaches include Brief Focal Psychotherapy [3]. Both brief and conventional psychotherapies demonstrate favorable immediate responses and maintain effectiveness over extended follow-up periods [4,5].

A limitation that has been described in structured models of brief psychotherapy is the reduced capacity to produce broader modifications in core psychological functioning, mainly due to the emphasis on the primary presenting complaint, the restricted duration of treatment, and the time required for participants to develop new skills capable of influencing deeper emotional and behavioral patterns [6,7].

The BATF was developed with the aim of promoting broader changes in emotional, cognitive, and behavioral functioning; however, these effects remain hypothetical and will be empirically evaluated in the present randomized controlled trial. In response to this gap, the present study proposes to evaluate a brief psychotherapeutic intervention that targets the primary complaint and is hypothesized to produce broader functional changes compared to an established brief psychotherapy. This study may contribute to the development of brief psychotherapeutic approaches.

BATF is a manualized and structured brief psychotherapeutic intervention currently under empirical evaluation. BATF is proposed to differ from existing brief psychotherapies by its procedural architecture, which operationalizes affect as a structured input for behavioral planning through a fixed sequential system of affective identification, thematic consolidation, and behavioral translation. Unlike traditional brief psychotherapies focused on insight generation or focal conflict exploration, BATF emphasizes the systematic conversion of affective states into actionable behavioral outputs within a standardized protocol. The procedural sequence is identical across participants, with variability arising only from the individualized emotional content and behavioral goals generated within the protocol-guided framework.

BATF is based on the assumption that clinically relevant affective experiences may not be immediately accessible through reflective cognitive processing alone. The intervention proposes that psychological distress may be partially maintained by difficulties in identifying, organizing, and behaviorally integrating pre-reflective affective experiences. Rather than initially emphasizing interpretation or cognitive restructuring, BATF employs a structured sequence designed to facilitate direct observation of affective experiences in their immediate manifestation. Through sequential affective identification, thematic organization, and behavioral translation, the intervention seeks to increase the cognitive accessibility and functional integration of affective information. This process is hypothesized to facilitate behavioral planning, adaptive decision-making, and reduce maladaptive emotional reactivity. The central hypothesis underlying BATF is that the systematic organization of affective experiences increases their cognitive accessibility and behavioral integration, thereby facilitating adaptive action and reducing symptoms of anxiety and depression.

BATF was developed as a novel brief psychotherapeutic intervention and was not derived from Brief Focal Psychotherapy or any other established psychotherapeutic model. The intervention employs a structured sequence of affective identification, thematic organization, and behavioral translation designed to facilitate adaptive behavioral planning. Although BATF was not developed within any single traditional psychotherapeutic school, its procedural structure was informed by a phenomenologically oriented focus on the description of affective experience as immediately lived [8] and by the hypothesis that difficulties in identifying, organizing, and behaviorally integrating affective experiences may contribute to psychological distress. These principles were subsequently operationalized in BATF through a standardized sequence of affective identification, thematic organization, and behavioral translation designed for empirical evaluation. This rationale is broadly consistent with conceptualizations of emotion regulation that emphasize awareness, understanding, and behavioral integration of emotional experiences as relevant components of adaptive psychological functioning [9]. Its core procedural structure is described in the Supplementary Materials S1.1 to ensure reproducibility, treatment standardization, and protocol transparency. A more extensive technical and theoretical manual has been developed for therapist training purposes and will be reported in future publications following completion of clinical validation. To date, BATF has not been evaluated in randomized controlled trials. The current trial evaluates BATF in participants with anxiety and depressive symptoms, as these conditions were selected as the initial target population for empirical investigation. However, this study population does not define the theoretical or clinical scope of the intervention, which remains open to future empirical evaluation across other conditions. Additionally, the intervention has been designed to require fewer sessions than traditional brief psychotherapies, and its effects remain to be empirically tested.

The comparative analysis of the two brief psychotherapies in this study will be conducted using validated clinical questionnaires. Biological biomarkers will be collected as exploratory outcomes. This approach is supported by previous studies demonstrating that important advances in psychotherapy research involve combining clinical assessment instruments with biomarker evaluation. Effective treatments are expected not only to reduce symptoms but also to demonstrate measurable clinical significance [10].

Accordingly, exploratory biomarkers associated with stress regulation, immune-inflammatory activity, and neuroplasticity were included to complement clinical outcome assessment. These biomarkers were selected because previous studies have linked them to biological processes involved in anxiety and depressive symptoms, including hypothalamic–pituitary–adrenal axis functioning, inflammatory signaling, and neurobiological adaptation to psychological interventions.

To further characterize treatment effects, biomarkers may reveal dynamic molecular alterations associated with disease processes and clinical improvement; in this context, biomarkers such as cortisol may reflect normal biological processes, pathogenic alterations, or responses to therapeutic interventions [11] and are increasingly incorporated into clinical psychological research [12]. They are commonly used to evaluate treatment outcomes and monitor symptom progression alongside clinical rating scales [13].

In view of the foregoing, this study reports the protocol of a randomized controlled trial evaluating BATF, a novel brief psychotherapeutic intervention. BATF will be compared with Brief Focal Psychotherapy, an established brief psychotherapeutic approach widely used in clinical practice. The trial aims to evaluate the effects of BATF on symptoms of anxiety and depression and to explore associated clinical and biomarker outcomes.

## 2. Methods and Analysis

### 2.1. Trial Design and Registration

This protocol was registered on 6 November 2024, in the Brazilian Clinical Trials Registry (ReBEC) under the identifier RBR-10p45rdg (https://ensaiosclinicos.gov.br/rg/RBR-10p45rdg, accessed on 11 June 2024), where the Statistical Analysis Plan (SAP) is available. The Universal Trial Number (UTN) is U1111-1313-4499.

This protocol was developed in accordance with the SPIRIT 2025 Statement. The completed SPIRIT 2025 checklist is provided as Supplementary Material S1.2.

This study is a single randomized controlled trial with blinded outcome assessment, blinded biomarker analyses, and blinded statistical analysis.

The trial has a 2 × 2 factorial structure, defined by two intervention arms BATF vs. Brief Focal Psychotherapy) and two clinical conditions (anxiety vs. depression), resulting in four analytical cells. Participants will be randomized in a 1:1 allocation to intervention arms, with stratification by clinical condition.

The trial includes two pre-specified analytical phases within the same randomized dataset. Phase 1 is the primary confirmatory analysis, comparing BATF versus Brief Focal Psychotherapy with clinical conditions collapsed. Phase 2 is a pre-specified secondary factorial analysis, evaluating the effects of intervention, clinical condition, and their interaction within the 2 × 2 framework. Both phases were defined prior to trial initiation and registered prospectively, with no adaptive modifications or interim decision-making based on Phase 1 results. Publication of Phase 1 results will not influence recruitment, eligibility criteria, randomization procedures, outcome measures, sample size targets, or statistical methods for Phase 2, which will continue according to the prospectively registered protocol.

The design allows estimation of overall treatment efficacy while also enabling pre-specified evaluation of differential effects across clinical conditions within a single randomized controlled trial framework.

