### 2.5. Outcomes

The objective of this study is to evaluate the effects of a brief psychotherapeutic intervention, BATF, compared with Brief Focal Psychotherapy in reducing symptoms of anxiety and depression.

Outcomes include quantitative measures of depressive and anxiety symptoms, sleep quality, and exploratory salivary and blood biomarkers associated with stress, inflammatory processes, and neurobiological function.

The co-primary outcomes for Phase 1 are defined as the change from baseline (Week 0) to Week 13 in symptom severity within each diagnostic stratum, assessed using disorder-specific scales (MADRS for depressive disorder and HAM-A for anxiety disorder).

Clinical diagnoses will be established during baseline psychiatric and clinical evaluation according to DSM-5-TR criteria prior to randomization. Participants will be stratified according to their primary clinical condition (anxiety or depressive disorder) and randomized to one of the two psychotherapeutic interventions. Each participant will be assessed only with the symptom severity scale corresponding to their primary diagnosis.

Secondary outcomes include depressive and anxiety symptom severity assessed using disorder-specific instruments according to participants’ primary clinical condition (PHQ-9 for depressive disorders and GAD-7 for anxiety disorders). Sleep quality, assessed using the Pittsburgh Sleep Quality Index (PSQI), and exploratory biomarker analyses will be performed in all participants.

Exploratory outcomes include salivary and blood biomarkers. Salivary biomarkers include cortisol, glutamate, immunoglobulin A (IgA), lysozyme, melatonin, alpha-amylase, chromogranin A, and fibroblast growth factor 2 (FGF2). Blood biomarkers include cortisol, pro–brain-derived neurotrophic factor (pro-BDNF), mature BDNF, sex hormones, dehydroepiandrosterone (DHEA), C-reactive protein (CRP), growth hormone, and glutamate. Cortisol and glutamate will be assessed in both saliva and blood samples. All biomarkers are pre-specified in the Statistical Analysis Plan and will be considered exploratory and hypothesis-generating.

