#### 2.10.2. Sample Size for Second Phase

The second phase of the clinical trial will require a larger sample size. Upon reaching 156 participants, the initial results comparing the two psychotherapies (experimental and active comparator groups) will be published. The research methodology will remain unchanged, but the second phase aims to assess the effect of condition across four distinct groups (BATF for depression, BATF for anxiety, control for depression, and control for anxiety).

An Analysis of Variance (ANOVA) will be employed for this comparison. The sample size calculation for this phase requires a total of 472 participants. Therefore, an additional 316 participants need to be recruited, with 79 participants in each of the four groups. This requirement accounts for the data from the initial 156 participants, which will be included in the evaluations for the second phase to achieve the total sample size of 472 for comparison across the four groups.

The sample size calculation for Phase 2 was based on a 2 × 2 factorial design with four equally sized groups, assuming balanced allocation across conditions (*n* = 118 per cell in the final sample). The calculation maintained the same statistical assumptions as Phase 1. No formal interim adjustments were planned, and the design assumes complete case availability at the final analysis stage. Importantly, no attrition (dropout) rate was included in the sample size calculation, which may result in reduced effective statistical power if loss to follow-up occurs during the trial.

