### 2.11. Statistical Methods

The primary analysis (Phase 1) will compare BATF versus Brief Focal Psychotherapy in a combined sample of participants with anxiety and/or depressive symptoms, irrespective of diagnostic category (“collapsed” clinical conditions). This analysis represents the primary confirmatory comparison of the trial.

Exploratory subgroup analyses within Phase 1 are pre-specified and will evaluate treatment effects separately in participants with anxiety and depressive symptoms.

The secondary analysis (Phase 2) will examine a pre-specified 2 × 2 factorial analytical framework (intervention × clinical condition), allowing assessment of main and interaction effects across four groups (BATF-depression, BATF-anxiety, control-depression, and control-anxiety), resulting in four analytical cells for the 2 × 2 factorial analysis.

For Phase 1, the primary comparison between BATF and Brief Focal Psychotherapy will be performed using Student’s *t*-test for normally distributed change scores or the Mann–Whitney U test when normality assumptions are not met. The first phase will include 156 participants.

Phase 2 will include a total sample of 472 participants (including participants from Phase 1 plus additional recruited participants). Change scores will be compared across the four predefined groups (BATF-depression, BATF-anxiety, control-depression, and control-anxiety) using one-way analysis of variance (ANOVA) or the Kruskal–Wallis test, as appropriate.

Assessments performed at Week 4 will be used to describe intermediate clinical evolution and may support exploratory analyses of treatment trajectories.

Effect Size Measure: Omega squared (ω^2^); Statistical Significance Level: α = 0.05.

Multiplicity for the co-primary outcomes will be controlled using the Holm–Bonferroni procedure. Secondary and subgroup analyses will be considered exploratory and interpreted accordingly. Exploratory biomarker analyses will apply false discovery rate (FDR) correction according to the Benjamini–Hochberg method.

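### Phase 2 sets out to assess an effect of clinical condition as part of a factorial structure, but condition is a baseline diagnosis, and the planned four-group test does not separate that observational contrast from the randomised ones

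*Protocol article*

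**What the plan says.** Section 2.1 gives the design as follows: "The trial has a 2 × 2 factorial structure, defined by two intervention arms" and two clinical conditions. The next sentence describes the allocation: "Participants will be randomized in a 1:1 allocation to intervention arms, with stratification by clinical condition". The same section gives Phase 2 the task of "evaluating the effects of intervention, clinical condition, and their interaction within the 2 × 2 framework".

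Section 2.5 fixes when and how condition is set: "Clinical diagnoses will be established during baseline psychiatric and clinical evaluation according to DSM-5-TR criteria prior to randomization". It continues: "Participants will be stratified according to their primary clinical condition (anxiety or depressive disorder) and randomized to one of the two psychotherapeutic interventions". It then adds: "Each participant will be assessed only with the symptom severity scale corresponding to their primary diagnosis".

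Section 2.10.2 states the purpose of the enlarged sample of 472 differently from Section 2.1: "the second phase aims to assess the effect of condition across four distinct groups", the groups being the four intervention-by-condition cells.

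Section 2.11 promises main and interaction effects. The test it names compares change scores across the four cells "using one-way analysis of variance (ANOVA) or the Kruskal–Wallis test, as appropriate". Neither that section nor the limitations in the Discussion says that a comparison between the two conditions is non-randomised.

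**The concern.** In a factorial trial both factors are assigned at random. Here one factor is assigned and the other is the diagnosis with which the participant arrives. Crossing the two gives four analysis cells, but randomisation balances nothing between the diagnoses. A difference in change between anxiety and depression participants therefore has no protected interpretation, whatever test is used.

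The instrument adds a second problem. On MADRS and HAM-A, and on PHQ-9 and GAD-7, condition and scale coincide completely, so a condition difference in change score may be only a difference between scales. The Pittsburgh Sleep Quality Index and the biomarkers, which are measured in everyone, escape this second problem but not the first.

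At stake is what a significant Phase 2 result would mean. Phase 2 takes recruitment from 156 to 472. If it is reported as the factorial result of a randomised trial, readers could take a diagnosis or scale difference for a finding that randomisation supports.

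**Working it through.** **1. What is randomised.** Sections 2.1 and 2.5, set side by side, give one randomised factor (intervention, 1:1) and one stratification factor (primary condition, diagnosed before randomisation). Sections 2.7 and 2.11 repeat the stratification. That is a two-arm parallel trial stratified by condition.

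**2. The plan's own sample sizes.** Inputs from Section 2.10: difference 5, SD 11, two-sided alpha 0.05, power 80%, 1:1 allocation.
- Phase 1, normal approximation: n per group = 2 × (1.960 + 0.842)² × 11²/5² = 7.85 × 9.68 ≈ 76. The *t*-test version gives 77, as the protocol states.
- Phase 2: the stated 472 (118 per cell) is recovered only if alpha is divided by 6, for all six pairwise comparisons of four cells: 2 × (2.638 + 0.842)² × 121/25 = 12.11 × 9.68 ≈ 117.2, so 118 per cell and 4 × 118 = 472. The *t* version gives 119 per cell, 476 in total. The division by 6 is an inference; the protocol does not state it.
- At alpha 0.05 the variants tried do not give 472. Pairwise comparison gives 304 to 308. The four-group ANOVA with a 5-point range gives 216, 286 or 427, depending on the pattern of means. A 5-point interaction gives 610.
- Of the six pairs of cells, two compare BATF with the comparator within a condition and are randomised. The other four cross diagnoses and are not.

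**3. What the planned test responds to.** Assume no treatment effect and no interaction, 118 per cell (N = 472), SD 11 on both scales, and a difference of D points in mean change between the diagnoses. Then f = (D/2)/11, the noncentrality is λ = N × f², and the one-way ANOVA has 3 and 468 degrees of freedom.

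| Assumed D (points) | f | λ | Probability of rejecting at 0.05 |
|---|---|---|---|
| 1 | 0.045 | 0.98 | 0.11 |
| 2 | 0.091 | 3.90 | 0.35 |
| 3 | 0.136 | 8.78 | 0.70 |
| 4 | 0.182 | 15.60 | 0.93 |
| 5 | 0.227 | 24.38 | 0.99 |

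The documents give no value for D; the table shows a range. SD 11 is given for MADRS only.

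**4. What the randomised contrasts can do at 472** (same SD, 5-point effect, alpha 0.05).
- BATF versus comparator within one condition, 118 versus 118: power about 94%.
- BATF versus comparator overall, 236 versus 236: power above 99%.
- Interaction: standard error 11 × √(4/118) = 2.03, so power for a 5-point difference of differences is about 69%.

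The sample therefore serves the within-condition treatment contrasts well and the interaction moderately, without any test of condition itself.

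**The case against.** The strongest reply is that factorial here describes the analysis. Sections 2.1 and 2.11 speak of analytical cells and an analytical framework, the allocation sentence follows at once, and nowhere is condition said to be randomised. This stands: a reader might infer that the protocol claims to randomise condition, and it does not. The label still attaches to the trial, and Section 2.10.2 still words the aim as the effect of condition.

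It is also fair to say that the right question is already planned. Section 2.1 lists the interaction and the evaluation of differential effects by condition, and Section 2.11 repeats main and interaction effects. A reader of Section 2.10.2 alone might infer that Phase 2 ignores effect modification; the other sections rule that out. What remains is that Section 2.10.2 states a different aim and that the named one-way test isolates none of these effects.

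Three further inferences are not supported:
- That the 316 additional participants are recruited for a condition main effect. A 5-point main effect of condition would need about 154 in total, and Section 2.10.2 sizes the phase for a four-group comparison.
- That the rejection probabilities are 84% at 3 points and 50% at 2. Those belong to a 236-versus-236 test of condition alone. The test named in Section 2.11 gives about 70% and 35%.
- That the diagnoses are known to differ in natural course, medication, sex mix or severity. The documents give no such data, and the point does not need it.

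Finally, rejecting when the diagnoses truly differ is power and not a type I error. That is correct. The fault lies in what the rejection would be taken to show.

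**Conclusion.** The point holds in limited form. The design label and the aim in Section 2.10.2 present a non-randomised contrast as one of the trial's effects, without saying that it is non-randomised, and on the primary scales that contrast is inseparable from the instrument. The planned one-way test can be significant from diagnosis or scale alone: probability about 0.35, 0.70 and 0.93 for differences of 2, 3 and 4 points. These figures rest on the assumed differences, a common SD of 11 and no treatment effect.

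A reader might go further and conclude that the trial's main result is compromised. The documents do not support that. Phase 2 is secondary, secondary analyses are declared exploratory, and neither the Phase 1 comparison nor the BATF-versus-comparator contrast within each stratum loses the protection of randomisation through this point. The change should be made because it alters what Phase 2 can conclude and costs very little.

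**What to change.** - In Section 2.1, describe a two-arm parallel trial stratified by clinical condition.
- In Section 2.10.2, bring the Phase 2 aim into line with Section 2.1: the BATF-versus-comparator effect within each condition, and whether it is modified by condition (the interaction).
- In Section 2.11, base Phase 2 conclusions on those contrasts in place of the four-group omnibus test. Keep condition in the model only as the stratification factor. Report outcome by condition descriptively and call it non-randomised. Because the interaction sets a MADRS difference against a HAM-A difference, state the metric on which it will be read.

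The cost is wording and one fewer tested effect. Participants, visits and data are untouched. Recruitment is planned to begin in the fourth quarter of 2026, so on that timetable the change can be made before any outcome data exist.
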